### Trial design {8}

This study is a phase I, two-arm, 1:1, randomized, triple-masked, placebo-controlled clinical trial.

## Materials and methods

### Study setting {9}

All clinical visits, including screening and informed consent, will be conducted in an academic clinic at the Helfgott Research Institute in Portland, OR.

### Eligibility criteria {10}

Eligibility criteria can be found in Table 4. Diagrammatic and tabular explanations of the overall trial design, flow of study procedures, and detailed study visit descriptions can be found in Figs. 1 and 2 and Table 3, respectively.

**Fig. 1 Fig1:**
[figure not shown]
Enrollment and allocation

**Fig. 2 Fig2:**
[figure not shown]
Flow of study procedures

**Table 3 Tab3:** Criteria for inclusion and exclusion

Inclusion criteria	Exclusion criteria
• Males and females aged 21–50 years • BMI 20–30 • Willing to be randomized to take isolated xanthohumol as a dietary supplement (or placebo) for 8 weeks • Willing to have blood drawn every 2 weeks and fast for 10–12 h before blood draws • Willing and able to collect stool samples at home every 2 weeks • Able to speak, read, and understand English • Must be able to provide written informed consent • Non-smokers (including tobacco and cannabis products, combusted or vaporized) *Permitted concomitant care or intervention during the trial:* • Use of over-the-counter medications as indicated on the label • Multi-vitamin/multi-mineral products • Dietary supplements except as detailed in exclusion criteria	• History of any chronic disease • Consumption of more than 1 microbrew beer per day • Typical intake of more than 2 alcohol-containing beverages per day, more than 14 per week, or more than 4 in any single day within 28 days prior to screening • Use of NSAIDs more than once per week for headaches, routine aches/pains, etc. • Use of any prescription drugs, including oral contraceptives (due to potential interference with mechanisms under investigation) • Acute viral or bacterial infection, or recent infection within 14 days prior to screening or still requiring prescription medication for treatment • Engaging in vigorous exercise more than 6 h per week • Women who are lactating, pregnant, or planning pregnancy during the study period • Within 3 months of screening: ° Use of prescription opioids for any reason ° Use of prescription corticosteroids for any reason ° Hospitalization (for any reason other than an elective medical procedure) ° Gastrointestinal surgery • Current or within 30 days of screening: ° Intravenous nutrition support therapy ° Intake of anti-coagulant or anti-platelet prescription medications ° Intake of antibiotic, antiparasitic, or antifungal medications orally or intravenously ° Initiation of or changes to supplements or medications, an exercise regimen, or food plan ° Involvement in a significant diet or weight loss program, low-carb diet program, or very-low calorie liquid diet program ° Use of recreational drugs/substances ° Participation in another interventional research study ° Undergoing UV therapy • Within 14 days of screening: ° Recent acute trauma occurring within 14 days prior to screening ° Recent (within 14 days prior to screening) intake of any dietary supplements containing xanthohumol flavonoids, or other natural products typically taken to modulate inflammation including curcumin, turmeric, fenugreek, hops, rosemary, ginger, white willow, devil’s claw, fish oil (doses > 1 g/day), bioflavonoids, or quercetin

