## Assignment of interventions: allocation

### Sequence generation {16a}, concealment mechanism {16b}, implementation {16c}, blinding {17a}, and unblinding {17b}

Randomization will occur within 30 days of screening by blocking within the randomization sequence, with randomization stratified by biological sex. The initial randomization series will be generated using readily available electronic random sequence generators. The randomization “code” will be created by a staff member not involved in trial operations and kept in a sealed envelope with a signature across the label and dated the day of creation. This envelope will be kept in a dedicated study folder and locked in the office of the Research Integrity Officer or designee. Thirty-two opaque envelopes will be created, sequentially numbered include a designation of the code for the assigned intervention based on the randomization sequence, and signed across the seal. Masking of the interventions (i.e., xanthohumol or placebo) will be accomplished by engaging trained staff not involved in trial operations to label product bottles based on the randomization code. Product bottles will be stored in separate locked cabinets by code and maintained in a temperature-controlled environment, with temperature logged weekly to assess environmental stability. Upon confirmation of eligibility and consent, Study Coordinators will then open the next sequentially numbered envelope at the time of randomization, the envelope number will be recorded, and allocation (As “A” or “B”) disclosed to both participant and coordinator for the first time, and the corresponding product will be removed from its locker and dispensed in the bottle to the participant. Thus, the trial will be triple-masked without PIs, co-investigators, study coordinators, or participants knowing allocation assignment of study participants. Unmasking is permissible if the DSMB requires it upon review and in the case of a serious adverse event.

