### Laboratory analysis outcomes {12}, statistical methods {20a, 20b, 20c}

Relevant laboratory-based safety measures were chosen as the primary safety outcomes, because this trial is intended to precede a clinical trial in adults with Crohn’s disease—a clinical population potentially vulnerable to anemia, liver toxicity, renal abnormalities, etc. Therefore, a formal assessment of laboratory changes in healthy humans provides critical information to guide expectations for changes in laboratory markers and associated adverse clinical effects in future research in Crohn’s and other clinical populations.

The primary objective’s laboratory-based outcome domains (and corresponding measures) are liver function (AST, ALT, alkaline phosphatase, bilirubin), renal function (BUN, creatinine, estimated glomerular filtration rate), hematology (red blood cell count, hematocrit, hemoglobin, white blood cell count), and electrolytes (sodium, potassium, calcium, chloride) measured every 2 weeks for 8 weeks. The primary outcome metric for comparison between study groups is the mean change from baseline to week 8. However, all parameters will be similarly evaluated at each follow-up time point, by formally comparing mean change from baseline to follow-up between groups. Comparisons at a single follow-up will use 2-sided independent *t* tests; omnibus tests for differing trends over time will employ linear mixed models with time point as a repeated factor and study group as an independent factor.

Primary outcome laboratory measures will be analyzed by first assessing descriptive statistics including mean, median, and standard deviation. All distributions will be tested for skew and transformed (e.g., natural log transformed) as needed to reduce the influence of skew in subsequent analyses. If inspection of distributions indicates significant non-normality that cannot be corrected with standard transformations, significance will instead be calculated using a non-parametric Wilcoxon signed rank test. The primary analysis will be a per-protocol analysis as this trial is a phase I trial focused on clinical toxicity, not a definitive efficacy or effectiveness trial; therefore, we are investigating the clinical and mechanistic effects of the product for those participants who took the experimental agent only. As a sensitivity analysis, missing laboratory data will be imputed by multiple imputation to assess the robustness of study results to imputation.

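### The 14-day infection, trauma and supplement windows look back from screening, but change is measured from a baseline that may fall up to 30 days later

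*Protocol article*

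**What the plan says.** All of the dated exclusions in Table 3 use screening as their reference point, but they are worded in two ways.

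- **Explicitly looking back.** The infection item reads "Acute viral or bacterial infection, or recent infection within 14 days prior to screening or still requiring prescription medication for treatment". The supplement item reads "Recent (within 14 days prior to screening) intake of any dietary supplements containing xanthohumol flavonoids" and goes on to list other products taken to modulate inflammation. Recent trauma carries the same 14-day look-back, and the alcohol item looks back 28 days before screening.
- **No stated direction.** One block is headed "Current or within 30 days of screening" and covers antibiotics, changes to supplements, medication or diet, recreational drugs and other trials. Another reads "Within 3 months of screening: ° Use of prescription opioids for any reason ° Use of prescription corticosteroids for any reason", followed by hospitalisation and gastrointestinal surgery.

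Some wording carries no date: the acute-infection and still-on-prescription parts of the infection item, and "Use of any prescription drugs, including oral contraceptives (due to potential interference with mechanisms under investigation".

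On timing, the allocation section ({16a} to {17b}) states "Randomization will occur within 30 days of screening". The screening and consent section makes baseline a separate visit with its own consent. The statistical methods section says "The primary outcome metric for comparison between study groups is the mean change from baseline to week 8". It also restricts newly abnormal laboratory values to those normal at baseline, and bases the cytokine and permeability effect sizes on change from baseline.

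**The concern.** Entry windows of this kind keep recent illness and recent anti-inflammatory exposure out of the reference sample. Here they protect the screening date, while the reference sample is the baseline one. A person can screen clean, have a viral infection on days 20 to 26, recover, and be randomised on day 28. The infection is over at baseline and was not in the 14 days before screening, so the criterion as worded does not exclude that person. The same can happen with a listed supplement started after screening and stopped before baseline.

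Two things are at stake. First, white cell count, TNF-α, other cytokines or calprotectin may be displaced at baseline, and their return to usual levels would be recorded as change on treatment. Second, a laboratory value that is transiently abnormal at baseline cannot later count as newly abnormal, so safety information on that parameter is lost for that participant.

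**Working it through.** The plan states no figure to reproduce, so the check is date arithmetic.

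**Inputs.** Window length w is 14 or 28 days (explicit look-back), or 30 days or 3 months, taken as 90 days (direction unstated), all from Table 3. The gap g from screening to baseline is 0 to 30 days, from the allocation section. That baseline samples are taken at or near randomisation is inferred from the order of consent and allocation; the participant timeline (Table 4) is not reproduced.

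**Formula.** A look-back of w days from screening covers days g to g + w before baseline. The last g days are uncovered, so the unprotected share of the w days before baseline is min(g, w)/w.

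| Gap g (days) | 14-day items | 28-day alcohol item | 30-day items, if looking back | 3-month items, if looking back |
|---|---|---|---|---|
| 0 | 0% | 0% | 0% | 0% |
| 7 | 50% | 25% | 23% | 8% |
| 14 | 100% | 50% | 47% | 16% |
| 21 | 100% | 75% | 70% | 23% |
| 30 | 100% | 100% | 100% | 33% |

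At the full 30-day gap, a 14-day window covers days 30 to 44 before baseline and nothing nearer.

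**How many people.** The documents give no infection rate. Assume r = 1 to 3 acute infections per adult per year.

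- Gap of at least 14 days: P = 1 − exp(−14r/365), giving 3.8%, 7.4% and 10.9% for r = 1, 2 and 3. Over 24 to 32 participants this is 24 × 0.038 = 0.9 to 32 × 0.109 = 3.5 people.
- Gap of 7 days: P = 1 − exp(−7r/365), giving 1.9%, 3.8% and 5.6%, or 24 × 0.019 = 0.5 to 32 × 0.056 = 1.8 people.

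These are upper bounds for their gap, because they include infections still acute at baseline, which the undated wording excludes.

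**Effect on an arm mean.** One participant whose change is displaced by D moves the arm mean by D/12 = 0.083D or D/16 = 0.0625D. With the SD held fixed, reaching the plan's Cohen's d threshold of 0.5 through one person alone would need D = 0.5 × 12 = 6 SD or 0.5 × 16 = 8 SD. Two such people in the same arm would need 3 or 4 SD each. A stray participant adds to the noise but would rarely produce a signal alone.

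**The case against.** The strongest reply is that the protocol already rechecks. The participant timeline section repeats the interview to confirm the criteria, and the allocation section confirms eligibility before the envelope is opened. The adverse event questionnaire, given at screening and baseline, would probably record an illness in between. This stands for anything current: acute infection, infection still on prescription treatment, and prescription use carry no date. It does not stand for an infection that has resolved, because the recheck applies criteria that say prior to screening, and recording an illness does not exclude or delay anyone.

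A reader might infer that every washout in Table 3 fails in this way. The documents do not support that. The 30-day and 3-month blocks do not say which way they run. Read in both directions, they cover the whole gap. On that reading, the item on starting or changing supplements would also catch a listed supplement begun after screening. Supplements are restricted during the trial as well, though the article does not say whether that includes the screening-to-baseline interval. The infection and trauma items have no such second reading.

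A reader might also infer bias between the arms. That does not follow either: these exposures precede randomisation and are independent of arm. Nor is every outcome a change score. Adverse events are compared by frequency, and no change-from-baseline analysis is set for the microbiome. The cytokine and permeability results are declared preliminary. The week 8 sample, the other half of the primary contrast, is not protected by any entry window, so re-dating removes only part of this noise.

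Finally, the article condenses a fuller protocol, and the usual interval or a rescreening rule may be set there. That bears on how often the gap arises, but not on the anchor that Table 3 states.

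**Conclusion.** The point holds in a limited form. The 14-day infection, trauma and supplement windows, and the 28-day alcohol item, are dated back from a visit that may precede baseline by up to 30 days. From a 14-day gap onward, the 14-day windows protect none of the 14 days before baseline; with a same-day baseline nothing is lost. The 30-day and 3-month items share the problem only if they look back, and that ambiguity itself should be settled.

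The consequence is added variability or chance imbalance in arms of 12 to 16, plus lost newly-abnormal information where a baseline value is transiently abnormal. It is not systematic bias. The number affected is unknown. The 4% to 11% range for infection is an upper bound that rests on an assumed rate and on a gap of at least 14 days for everyone. This is an inexpensive improvement and does not threaten the trial's validity.

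**What to change.** Keep each window's length, but date it from the baseline/randomisation visit, or state that it runs from the present look-back through that visit. Give the 30-day and 3-month blocks an explicit direction at the same time. Apply the re-dated windows in the eligibility confirmation already made before the envelope is opened. Let a participant who fails only a time-limited item have the baseline visit delayed until the window clears, with rescreening if the 30-day limit is passed.

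The uncovered period then falls from as much as 30 days to 0, and the planned sample size does not change. The cost is a few delayed or repeated visits and a wording amendment. That amendment goes to NCCIH (whose approval is needed before implementation), the FDA and the IRBs. Since recruitment began on August 15, 2019, a change made during recruitment would leave some participants enrolled under the old wording, which should be noted in the report.

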
### Screening and informed consent {26a, 26b}, confidentiality {27}

Measures to ensure the privacy of information on study participants will be maintained throughout the trial. All study investigators and staff are certified in Good Clinical Practices, Human Subjects Research, and Responsible Conduct of Research and have received training in clinical HIPAA regulations. Telephone screening will be conducted via verbal interview to assess inclusion and exclusion criteria noted in Table 4. Eligible participants will then be invited to an in-person, clinical screening visit. Screening informed consent will be collected from all participants at the screening clinical visit and cover collection and storage of medical history as well as collection and analysis of biological specimens. Trial informed consent will be collected from all participants at the baseline clinical visit and will review the collection and analysis of biological specimens, the option to supply additional samples to be stored for future research purposes, and all other trial operations.

**Table 4 Tab4:**
[figure not shown]
Participant timeline

## Interventions

### Intervention description {11a} and choice of comparators {6b}

Participants randomized to xanthohumol will be administered 24 mg of 99+% pure xanthohumol combined with 288 mg of rice protein, 109.3 mg microcrystalline cellulose, 4.3 mg Aerosil® 200 fumed silica, and 4.3 mg magnesium stearate, in an orange capsule to maintain masking. Xanthohumol has been combined with a rice protein carrier as this has been shown to significantly improve xanthohumol bioavailability in human subjects [26]. Participants randomized to placebo will be administered 288 mg of rice protein, 133.4 mg microcrystalline cellulose, 4.3 mg silica, and 4.3 mg magnesium stearate combined in an identical capsule. Xanthohumol is considered odorless and the capsules produce no residue.

### Criteria for discontinuing or modifying allocated interventions {11b, 21b}

A participant may be withdrawn from the trial at any time they choose, due to adverse events or at their request. However, participants will be actively withdrawn if they demonstrate any new onset, moderate, or more severe adverse events attributable to the intervention. Participants will also be withdrawn if they have any critical value return on routine clinical laboratory measures of safety, including significant changes in blood cell counts, liver function tests, or renal function tests. The trial will be suspended if > 20% of study participants experience moderate or greater severity adverse events or laboratory abnormalities contributing to halting criteria including abnormal calcium, sodium, potassium, creatinine, or GFR; anemia; and/or abnormal elevations in bilirubin, elevated alkaline phosphatase, AST, or ALT that are persistent upon repeat testing.

### Adherence to intervention {11c}

Data on adherence to the treatment protocol will be assessed by study product return and pill counts at the week 4 and week 8 clinical visits. Participants will be informed that the returned study product will be counted to determine adherence to the protocol. Each visit will include verbal queries regarding any missed doses, extra doses, or lost capsules in order to be able to account for all study product. Study coordinators are trained to encourage use of reminder alarms and/or other tips to encourage adherence, as needed. Taking at least 80% of the required doses will be considered adherent.

### Relevant concomitant care permitted or prohibited during the trial {11d}

See Table 3.

### Provisions for post-trial care {30}

All randomized study participants who take the study product will be instructed to report adverse events to the trial investigators for 30 days following their discharge from the trial. Any new-onset adverse event not established at screening or during the trial, whether reported spontaneously or at the closeout clinical visit, will be followed up on via telephone by the study coordinator to determine its outcome. Throughout the study, if laboratory values, vital sign measurements, or self-reported adverse events arise, the study team will expediently make referrals to a primary care provider or to mental health crisis resources in Portland, OR. Because the experimental drug contains only a compound considered Generally Recognized as Safe, and is readily available in the diet, no serious harms are anticipated upon discontinuation of the drug that would require medical intervention.

### Participant timeline {13} and data management {19}

All clinical visits, including screening and informed consent, will be conducted at the Helfgott Research Institute in Portland, OR. Verbal interviews will be repeated to confirm participation criteria are met. During the clinical screening visit, salivary HIV screening and urinary pregnancy tests will be performed by study staff, as well as a series of anthropometric measurements, vital signs, medication usage, blood samples, and recent adverse event history for later comparison as stated in Fig. 2 and Table 3.

Data collected from clinical screening visits and throughout the study period will be maintained as both paper case report forms (CRFs) and electronic copies entered into a Research Electronic Data Capture (REDCap) [27] database in a de-identified manner on a password-protected tablet by study staff. During baseline visits, study staff will verbally administer questionnaires for adverse events, collect vital signs and anthropometric values, and administer the Patient-Reported Outcomes Measurement Information System (PROMIS-29) questionnaire which measures health-related quality of life across disease categories [28]. Data entered for adverse events and PROMIS-29 will be considered final data as the study team member conducting the visit will be entering those results directly into the REDCap database. All other data initially recorded into REDCap will be marked as “unverified” within the system to later be confirmed by a member of the study team, additionally regulated in REDCap by implementing specified allowable ranges of input to minimize the chance of data entry errors, as systems of quality control. Additional methods for ensuring confidentiality and data protection are outlined below.

For every clinical visit, specimen collection including 24-h urine and stool collection will occur as outlined in Table 4. During their time enrolled in the study, participants will be expected to take one capsule of the assigned product daily and record of any emerging symptoms to be collected at their next clinical visit. All adverse event reports will be collected through case report forms (CRFs) and documented in REDCap database for Data Safety Monitoring Board (DSMB) monitoring and post-trial analysis.

### Sample size {14}

A sample size of twenty-four (*n* = 12 per group) provides 80% power to detect a 50% difference in proportions of participants between groups by chi-squared test experiencing a laboratory abnormality or adverse event at a significance threshold of *α* = 0.05. To account for up to 25% attrition, up to 16 adults (8 biologically male and 8 biologically female participants) will be enrolled in each study arm. Given that this phase I trial is intended as a step toward a phase II clinical trial in Crohn’s disease, for which few effective treatments exist, the investigational drug is commonly available in the diet, and previous human studies have not suggested any toxicity, the present trial was powered to detect gross toxicity resulting in frequent adverse events and/or laboratory-measurable toxicity. However, interim halting criteria were also used to assess safety; an accumulated frequency of 25% reaching laboratory halting criteria was pre-specified as a criterion for halting the trial and requiring detailed review by the FDA, NCCIH, and IRB.

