As an element of the evaluation for safety of the intervention, the percentage of laboratory newly abnormal (for values that were within the clinically normal range at baseline) per clinical laboratory reference ranges for each lab parameter will be reported at each time point and the percentage will be compared between groups by Fisher’s exact test. Assessment for changes in the distribution of each lab parameter will be performed by presenting means and confidence intervals (CI) for the change in each group, as well as the mean CI for the difference between groups; significance will be tested using 2-sided, unpaired *t* tests (or, if inspection of distributions indicates strong non-normality, with a non-parametric Wilcoxon signed rank test) of the mean values for the xanthohumol group compared to the placebo group. Assessment for overall *increases* or *decreases* in collected parameters will be tested for linear trends of the means by linear mixed ANOVA, considered significant if *p* < 0.05, with time point as a repeated factor. This may be suggestive of evidence for cumulative toxicity if trending in a clinically deleterious direction.

Health-related quality of life, measured by PROMIS-29, is included as a tertiary measure of gross changes in health. PROMIS-29 includes 7 validated subscales (physical function, anxiety, depression, pain intensity, pain interference, sleep, social interactions), each of which will be calculated as a mean by group, and means will be compared between xanthohumol and placebo, with the primary comparison being of mean changes from baseline to week 8. Significance of changes in QOL measures will be tested according to the same plan outlined for laboratory markers, above.

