### Adverse event reporting and harms {22}

Adverse event monitoring will occur using a standardized, multi-system, 81-item adverse event questionnaire based on the National Cancer Institute’s Common Terminology Criteria for Adverse Events. The adverse event questionnaire will be administered verbally by study staff at each of the clinical visits, including the initial screening visit, with a query to determine if other symptoms not elicited by the questionnaire have been experienced. Participants will be encouraged to contact study staff between study visits if they are experiencing any new, unusual, or bothersome symptoms. Adverse events reported between study visits (i.e., not reported on the 81-item adverse event interview during scheduled visits) will be termed a “spontaneous report” adverse event and will be documented within the participant’s file by the study staff to capture the severity/grade of the report, any clinical actions taken, and the current state of the adverse event. Following a spontaneous report, the study team, in coordination with a participant’s physician as needed, will develop a response or monitoring plan, which will also be documented.

All reported adverse events, as well as the length of duration, will be reported upon trial completion with a comparison of frequency between groups. Attributability to the intervention will be determined on a case-by-case basis by the clinical investigators and DSMB members according to accounts of the event(s) in previous research, whether the symptom was present at baseline, the severity and clinical trajectory of the symptom (i.e., did it worsen with accumulated exposure), whether similar symptoms accumulated in one group vs. another, and/or if the symptom was subjectively attributed to another cause *by the participant* (e.g., wrist pain following an injury at work).

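### The stated 80% power is for a chi-squared test of a participant-level composite that the analysis section never tests; the declared primary metric, mean change to week 8, has no stated power

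*Protocol article*

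**What the plan says.** In the Protocol article, Sample size {14} rests the trial size on one calculation: a total of 24 participants, 12 in each arm, "provides 80% power to detect a 50% difference in proportions of participants between groups by chi-squared test experiencing a laboratory abnormality or adverse event". The threshold is α = 0.05. No placebo rate is given, and the section does not say whether the test is one- or two-sided. Enrolment is raised to 16 per arm for attrition of up to 25%. The same section then describes the trial as powered for gross toxicity.

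The section on laboratory outcomes and statistical methods {12, 20a–c} sets out different comparisons:

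- "The primary outcome metric for comparison between study groups is the mean change from baseline to week 8", for 15 laboratory measures in four domains, by two-sided independent t tests, with mixed models for trends over time.
- The percentage newly abnormal, "per clinical laboratory reference ranges for each lab parameter will be reported at each time point and the percentage will be compared between groups". The test named for this is Fisher's exact test.

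Adverse event reporting and harms {22} says that events are collected "using a standardized, multi-system, 81-item adverse event questionnaire" at each visit, plus spontaneous reports. Their frequency is compared between groups, with no test named.

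**The concern.** A power statement tells the reader what a null result is worth, and it does so only for the analysis it describes. Here the endpoint (any laboratory abnormality or adverse event, counted once per participant) and the test (chi-squared) appear in the sample size section and in none of the stated analyses. The metric declared primary has no stated power.

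The consequence is practical, because the Hypotheses section treats a frequency that is not significantly higher on xanthohumol as part of the demonstration of safety. A reader could take non-significant results from the t tests or the per-parameter Fisher tests as 80%-powered evidence against gross toxicity, although the 80% was calculated for neither.

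**Working it through.** **Inputs.** From Sample size {14}: 12 per arm, 16 per arm before attrition, α = 0.05, and a 50% difference in proportions, read here as 50 percentage points. Allocation is 1:1 (Trial design {8}). The placebo rate p₁ is not documented, so it is varied from 0% to 50%, with p₂ = p₁ + 0.50. Two-sided tests are assumed unless stated.

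**Reproducing the plan's figure.** The pooled-variance formula is

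power = Φ[(Δ − 1.96·√(2p̄(1−p̄)/n)) / √((p₁(1−p₁) + p₂(1−p₂))/n)].

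At 5% vs 55%, p̄ = 0.30. The null standard error is √(0.42/12) = 0.187 and the alternative standard error is √(0.295/12) = 0.157. Then (0.50 − 0.367)/0.157 = 0.85, and Φ(0.85) = 80.2%. The stated 80% reproduces. The formula is symmetric, so 45% vs 95% also gives 80.2%. The minimum is at 25% vs 75%: (0.50 − 0.400)/0.177 = 0.565, or 71.4%. The attrition step also reproduces: 12/0.75 = 16.

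**Exact power.** This sums the binomial probabilities of all 2×2 tables that each test rejects.

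| Placebo vs xanthohumol | Chi-squared (uncorrected), n = 12 | Fisher, n = 12 | Fisher, n = 16 |
|---|---|---|---|
| about 0% vs 50% | 92.7% | 80.6% | 96.1% |
| 5% vs 55% | 83.1% | 69.2% | 85.5% |
| 10% vs 60% | 79.1% | 63.9% | 78.6% |
| 25% vs 75% | 76.6% | 60.8% | 73.7% |
| 40% vs 90% | 79.1% | 63.9% | 78.6% |
| 45% vs 95% | 83.1% | 69.2% | 85.5% |
| about 50% vs 100% | 92.7% | 80.6% | 96.1% |

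The first row can be checked by hand. With no placebo events, chi-squared rejects from 4 of 12 upwards and Fisher from 5 of 12. For X ~ Bin(12, 0.5), P(X ≥ 4) = 1 − 299/4096 = 92.7% and P(X ≥ 5) = 1 − 794/4096 = 80.6%.

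**The declared primary metric.** For a two-sided two-sample t test with α = 0.05 and 80% power, the noncentral t distribution gives a detectable standardised difference of about 1.20 SD at 12 per arm and about 1.02 SD at 16 per arm.

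**Background rate of the composite.** The listed measures are 4 liver + 3 renal + 4 hematology + 4 electrolytes = 15, taken at 4 follow-up visits, with an 81-item questionnaire and spontaneous reports added. The documents give no expected placebo rate for this. If it exceeds 50%, p₁ + 0.50 is greater than 1, so a 50-point excess cannot occur. As an illustration only, suppose every xanthohumol participant has an event. Two-sided Fisher power at 12 per arm is then 28%, 7% and 0.4% for assumed placebo rates of 70%, 80% and 90%.

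**The case against.** The strongest reply is that the 80% is not an arithmetic error, and that is right. A reader might infer that the figure holds only at a very low placebo rate. It does not: the pooled formula gives 80% again at 45% vs 95%, the unpooled formula gives at least 80.7% at every rate, and the one-sided pooled formula at least 82.4%. The exact power of the named test never falls below about 77% while a 50-point excess is possible.

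A reader might also infer that the planned Fisher test has only 61% to 69% power. The documents do not support that either. Fisher is planned for single laboratory parameters at single visits, not for the composite, so the range is what Fisher would give if it were applied there. It assumes a two-sided test and placebo rates of 5% to 45%. A one-sided Fisher test at 0.05 gives 77% to 83% over the same rates, and the plan does not state Fisher's sidedness.

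A third tempting inference is that the composite must have a high placebo rate. Treating the 15 measures as independent with 95% reference ranges and within-person correlation of 0.8 to 0.9, simulation gave 54% to 70% of placebo participants newly abnormal. With directional limits and correlated related measures it gave about 37% to 51%, and about 27% to 28% at within-person correlation 0.95. None of these assumptions is in the documents.

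It can also be said that an article condenses a fuller protocol, that the composite is close to the trial's hypothesis, and that the plan openly aims only at gross toxicity and adds halting criteria. A missing placebo rate, taken alone, would indeed be no finding. What stands is that the two sections, both in the text, state different endpoints and different tests.

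**Conclusion.** The point holds as a mismatch between the sample size and analysis sections. The 80% is attainable for the chi-squared test named, but that test and its composite are absent from the stated analyses, and the metric called primary has no stated power. On the same composite, a change to two-sided Fisher would take power at 12 per arm to about 61% to 69% for placebo rates of 5% to 45%, reaching about 81% only near 0% or 50%. With all 16 per arm retained it would be 74% to 86% for placebo rates of 5% to 45%. For mean change, the trial can detect only a large difference, about 1.2 SD at 12 per arm.

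These figures assume a 50-point absolute difference and two-sided α = 0.05. A high background rate is plausible for so broad a composite and would make the powered difference impossible above 50% on placebo, but that remains an assumption.

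**What to change.** Make both sections name the same participant-level comparison and the same test. Then restate the power for that test with the assumed placebo rate and sidedness. For example, two-sided Fisher at 10% vs 60% has 64% power at 12 per arm and 79% at 16 per arm. Add that the mean-change metric detects about 1.2 SD at 12 per arm, or about 1.0 SD at 16, with 80% power.

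The assumed placebo rate should be one the authors consider realistic for the composite as defined. Narrowing the composite would be a design choice, and correcting this mismatch does not require it.

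The cost is a rewritten sample size paragraph and one test added to, or clarified in, the analysis section. No extra participants are needed. The downside is that the stated power may be less favourable than 80%.
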